## Methods and analysis

### Study design

The BIOMIGA trial is a multidisciplinary, multicentric, open-label, controlled, interventional, prospective phase 4 study aimed at identifying candidate biomarker profiles associated with response to CGRP-targeting mABs, using exploratory multivariable and machine-learning approaches to integrate demographic, clinical, psychological, cognitive, epigenetic, pharmacogenetic, biochemical, and structural and functional brain imaging data. The trial was registered at ClinicalTrials.gov with the ID NCT04503083.

### Sample size calculation

In the absence of a reliable biomarker for predicting the response to antimigraine drugs, we considered, on an empirical basis supported by the limited available data, the difference in baseline methylation levels of CpG islands of the RAMP1 gene, a key receptor subunit of calcitonin gene-related peptide (CGRP), between migraine subjects who are responders and those who are non-responders to CGRP-targeting mABs.

The minimum sample size was inferred considering previous exploratory epigenome-wide association scans (EWAS) in migraine. Wan D. et al. (16) found that the methylation level of CpG islands of the RAMP1 gene, a key receptor subunit of CGRP, was significantly lower in females living with migraine than in healthy female volunteers (2.18% ± 1.91% vs. 5.85% ± 5.41%). Taking this variance into account, we computed a sample size of 47 participants per group (80% power, 5% significance level). Moreover, we considered a 6% loss of participants. Given the rate of >75% response to erenumab observed in randomised clinical trials (30%), as well as the rate of <25% response, we required a minimum sample size of 168 subjects with migraine at baseline and 51 controls.

This sample-size calculation was designed to support the proof-of-concept biomarker-discovery component of the study and was not intended to provide statistical power for definitive high-dimensional machine-learning model development. Therefore, machine-learning analyses are considered exploratory and hypothesis-generating, with the aim of reducing dimensionality and prioritising candidate multimodal predictors for future validation in larger independent cohorts.

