#### Descriptive and inferential statistics

All computations were conducted via *R* software (version 4.4.0). Quantitative variables were compared using the cross-sectional Mann–Whitney test, whereas categorical variables were assessed via the chi-square test or Fisher’s exact test. A value of *p* < 0.05 was considered statistically significant. The statistical plan included baseline comparisons between R and NR across clinical, anamnestic, psychological, and disability measures. Variables were also compared between healthy controls and migraine patients, stratified for gender and diagnosis. Predictive thresholds for circulating serum *α*-CGRP, IL-1β, and TNF-α levels were estimated in patients using binomial logistic regression (generalised linear model, GLM).

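### The 47 per group cannot be reproduced from the printed means, SDs, power and significance level, and no responder versus non-responder difference is given to support the 80% power

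*Protocol article*

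**What the plan says.** The section Sample size calculation sets out to size the difference in baseline RAMP1 methylation "between migraine subjects who are responders and those who are non-responders to CGRP-targeting mABs". Its numerical basis is an earlier epigenome-wide study in which methylation "was significantly lower in females living with migraine than in healthy female volunteers (2.18% ± 1.91% vs. 5.85% ± 5.41" percent. It continues "Taking this variance into account" and then states that "we computed a sample size of 47 participants per group (80% power, 5% significance level").

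The patient total follows from 47 in two steps: "we considered a 6% loss of participants", and "Given the rate of >75% response to erenumab observed in randomised clinical trials (30%), as well as the rate of <25% response", from which "we required a minimum sample size of 168 subjects with migraine at baseline and 51 controls".

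The section does not name the test, its sidedness, any adjustment for multiple comparisons, or a target difference for responders versus non-responders. Under Descriptive and inferential statistics the planned test is given: "Quantitative variables were compared using the cross-sectional Mann–Whitney test", with p < 0.05.

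**The concern.** Two things do not fit.

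- **Inputs and result disagree.** Two means, two SDs, a power and a significance level are printed beside a sample size, and the usual formulas applied to them do not return it.
- **The figures belong to another contrast.** The section says it sizes responders against non-responders, both of whom have migraine. The printed figures compare migraine with health. They come from women only, while the eligibility criteria admit both sexes.

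At stake is what the 80% means. Both totals, 168 patients and 51 controls, descend from 47. The responder contrast is the primary working hypothesis in the Aim section, whereas migraine versus control is listed among the secondary analyses. If the 80% is not tied to a stated responder difference, the article does not tell a reader what size of RAMP1 difference the study could reasonably have missed.

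**Working it through.** **Inputs (Sample size calculation).** Means 2.18 and 5.85; SDs 1.91 and 5.41; power 80%; level 5%; loss 6%; 30% in each extreme response group (the text gives 30% for >75% response, and I read the <25% share as the same). A two-sided test and 1:1 allocation are my assumptions.

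**Step 1: the printed effect.**
- Difference: 5.85 − 2.18 = 3.67 points.
- Combined SD: √((1.91² + 5.41²)/2) = 4.06.
- Standardised difference d: 3.67/4.06 = 0.905 (combined SD); 3.67/5.41 = 0.678 (larger SD); 3.67/1.91 = 1.92 (migraine SD).

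**Step 2: trying to reproduce 47.** The starting formula is n per group = 2(1.960 + 0.842)²/d², refined with the noncentral t distribution.

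| SD used | t-test n, 80% power | Mann–Whitney n* | Power at 47 for 3.67 points (t-test) |
|---|---|---|---|
| 4.06 (combined) | 20.2 → 21 | 22 to 24 | 99% |
| 5.41 in both groups | 35.1 → 36 | 37 to 41 | 90% |
| 1.91 in both groups | 5.4 → 6 | – | above 99% |

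*t-test n divided by a relative efficiency of 0.955 or 0.864.

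A Welch test with the two SDs kept separate gives 78.3% power at 20 and 80.4% at 21, so again 21. One-sided testing lowers every figure. A three-group analysis of variance at 80% power gives 19 to 43, depending on the SD and on where the third mean is placed. None of these gives 47. For 47 per group to have exactly 80% power for 3.67 points at a two-sided 5% level, the common SD would have to be 3.67/0.584 = 6.28, larger than either printed SD.

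**Step 3: what does give 47.** Two standard t-test routes do, each with SD 5.41 in both groups:
- 90% power at 5%: 46.6 → 47.
- 80% power at alpha 0.05/3: 46.96 → 47 (power at 47 is 80.04%).

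Each needs an input the section does not state.

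**Step 4: the later steps.** 47/0.30 = 156.7 → 157, and 157/0.94 = 167.02 → 168, as stated. For controls, 47/0.94 = 50 against 51 stated, a difference of one. The problem is confined to the 47.

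**Step 5: the responder contrast.** No difference is printed, so it has to be assumed. Power at 47 per group (two-sided 5% t-test), if the true difference is a fraction of 3.67:

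| Fraction of 3.67 | SD 1.91 | SD 4.06 | SD 5.41 |
|---|---|---|---|
| 75% (2.75 points) | above 99% | 90% | 68% |
| 50% (1.84 points) | above 99% | 58% | 37% |
| 25% (0.92 points) | 63% | 19% | 13% |

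**Step 6: what 47 per group detects.** At 80% power and a two-sided 5% level, d = 0.584. That is 0.584 × 1.91 = 1.1 points, 0.584 × 4.06 = 2.4 points, or 0.584 × 5.41 = 3.2 points. None of these is 3.67.

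**The case against.** The strongest reply is that 47 may be right and only its inputs undisclosed. The design yields three groups (>75% responders, <25% responders and controls), hence three pairwise comparisons. Holding 5% overall by Bonferroni, with the larger SD, gives 47 at 80% power. This stands as a possible explanation. It rules out any claim that 47 can never correspond to 80% power, or that an arithmetic slip has been proved. It does not repair the text, which states a 5% level and mentions no adjustment.

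Second, the section says only that the variance was taken into account. A reader might infer that the 3.67-point difference was carried over to responders versus non-responders, which would mean a gap of 1.9 migraine SDs between two groups of patients. The article does not say so. What can be said is narrower: the only printed difference belongs to another contrast, and if a different one was used it is not given.

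Third, 47 exceeds what the cited effect needs. That is correct, so a reader should not infer that the study is underpowered for that effect. It says nothing about the responder contrast, where power may be far below or far above 80% depending on the true difference and SD.

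Fourth, the section calls the calculation proof of concept and its basis empirical, and a condensed article may leave detail to the full protocol. The disclaimer, however, withdraws only the claim to power the machine-learning models; it leaves the 80% in place for biomarker discovery. Nor is this simply a matter of omitted detail: inputs and result are printed together and do not agree.

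**Conclusion.** Wrong as written, but not critical. At the stated 80% power and 5% level the printed means and SDs give 21 per group, or 36 with the larger SD throughout, against 47 stated. Power at 47 for the printed difference is 99% or 90%. These figures assume a two-sided t-test with equal groups; the planned Mann–Whitney test moves them to 22 to 24 and 37 to 41, still short of 47.

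The 80% is also not shown to apply to responders versus non-responders, because no difference for that contrast is given. The documents do not establish that the study is underpowered there: at half the cited difference, power runs from 37% to above 99% across the plausible SDs. They establish only that the claim has no stated basis.

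Severity is limited because 47 is more than the cited effect requires, the steps from 47 to 168 are coherent, enrolment is closed, and the primary objective is a classification panel rather than a RAMP1 test.

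**What to change.** Correct the sentence by stating the difference, SD, test, sidedness and alpha that actually produced 47. If they cannot be recovered, withdraw the claim that 47 follows from the cited figures.

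In either case add three things:

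1. What 47 per group delivers for the responder contrast: with a two-sided 5% t-test and 80% power, a standardised difference of 0.58, which is 1.1, 2.4 or 3.2 points at SD 1.91, 4.06 or 5.41.
2. A statement that the published difference between migraine and healthy women does not estimate the difference between responders and non-responders.
3. The detectable difference at the group sizes actually reached.

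The cost is one paragraph and no patients. The Status of the study section says processing for the stratified groups is still under way, so the correction can be made before those results are interpreted.

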### Subjects recruitment

Participants were recruited in three tertiary headache centres: C. Mondino Foundation in Pavia (Italy), Vall d’Hebron University Hospital/Vall d’Hebron Institut de Recerca (VHIR) in Barcelona (Spain) and Institut für Systemische Neurowissenschaften, Universitätsklinikum Hamburg-Eppendorf Hamburg (Germany).

Each centre enrolled a group of patients with HFEM or CM and a group of age- and sex-matched healthy subjects.

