At the coordinating centre in Barcelona, MRI data were acquired on two 3.0 T Siemens systems (Tim Trio and MAGNETOM Prisma, Siemens, Erlangen, Germany). The Tim Trio was equipped with a 32-channel phased-array head coil, whereas the MAGNETOM Prisma used a 64-channel head–neck coil. The acquisition protocol comprised: (1) a high-resolution 3D T1-weighted scan (MPRAGE; TR/TE = 2300/2.98 ms, FOV = 256 mm, 192 slices, voxel size = 1 mm^3^ isotropic); (2) resting-state fMRI (rs-fMRI) using a T2*-weighted GRE-EPI sequence (TR/TE = 2330/26 ms, voxel size = 2.0 mm^3^ isotropic, FOV = 224 mm, 34 slices, 305 volumes); (3) arterial spin labeling (ASL) using a 3D TSGE pCASL sequence (TR/TE = 3000/22.56 ms, TI = 1800 ms, FOV = 256 mm, 42 slices, 2 measurements [1 label/1 control], voxel size = 1.0 × 1.0 × 2.5 mm^3^).

In Hamburg, MRI data were acquired on a 3.0 T MAGNETOM Prisma scanner (Siemens Healthineers, Erlangen, Germany) equipped with a 32-channel head coil. The acquisition protocol comprised: (1) a high-resolution 3D T1-weighted scan (MPRAGE; TR/TE = 2300/2.98 ms, flip angle = 9°, 240 slices, voxel size = 1 mm^3^ isotropic, FOV = 256 mm); (2) resting-state fMRI (rs-fMRI) using a T2*-weighted GRE-EPI sequence (TR/TE = 2330/26 ms, voxel size = 2 mm^3^ isotropic, FOV = 256 mm, 34 slices, 305 volumes); and (3) arterial spin labeling (ASL), including a 3D TSGE pCASL sequence (TR/TE = 3000/22.56 ms, TI = 1800 ms, FOV = 256 mm, 42 slices, 2 measurements [label/control]) and an additional 2D pulsed ASL (PASL) sequence (TR/TE = 3000/12.0 ms, TI = 1800 ms, FOV = 256 mm, 21 slices, 90 measurements [45 label/45 control]).

To account for multicentric variability, scanner site was explicitly modelled as a covariate in all group-level neuroimaging analyses, and dedicated quality-control procedures were applied to ensure consistency of spatial coverage, artefact burden and temporal signal characteristics across centres. All datasets underwent local anonymisation and active defacing before central storage and processing.

Details of pre- and post-processing are going to be integrated in future publications.

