#### Mitigation of confounding factors

Given the real-world observational design of the BIOMIGA study, several measures were adopted to minimise the influence of potential confounding factors. Clinical outcome classification were based on prospectively collected headache diaries, which represent the reference standard for the assessment of migraine outcomes in real-world studies and reduce recall bias through systematic longitudinal recording of headache frequency and acute medication use (39). Standardised eligibility criteria limited major sources of confounding, including medication overuse headache, concomitant preventive treatments, severe neurological or psychiatric disorders, cardiovascular diseases, substance abuse, and other medical conditions potentially affecting biomarker levels or treatment response.

Demographic and clinical variables, including age, sex, migraine subtype, disease duration, baseline monthly migraine days, disability measures, acute medication intake, and relevant comorbidities, were systematically collected and evaluated as potential confounders. Analyses aimed at identifying clinically meaningful cut-offs for circulating CGRP concentrations were performed using GLM for prespecified clinical and demographic covariates to estimate independent associations while accounting for potential confounding. For epigenetic analyses, standardised procedures were adopted to minimise pre-analytical variability. Quality-control procedures and batch-effect correction methods were applied where appropriate, and known determinants of DNA methylation variability, including age, sex, medication exposure, and lifestyle-related factors such as smoking habits, were considered during statistical analyses to reduce potential confounding.

To reduce variability in neuroimaging-derived measures, MRI data were acquired using standardised acquisition protocols and processed through harmonised quality-control and preprocessing pipelines. Structural and functional MRI datasets underwent visual and automated quality assessment, with exclusion of scans affected by major artefacts or excessive motion.

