From a design standpoint, the open-label, non-randomised nature of the study is another important limitation. On the other hand, the stratification of patients by response to a target-specific drug represented a strong enough approach to assess response-related changes in multidisciplinary protocol. Of note, funding considerations were also important in the definition of the approach, since a placebo-controlled study would have required a larger population, a longer schedule and a more consistent funding. In addition, open-label observational designs allow inclusion of patients with high disease burden and multiple previous preventive failures, who are often under-represented in randomised controlled trials but represent a large proportion of those treated with CGRP mABs in routine practice. Future validation studies on larger populations and more stringent methodology are needed to confirm the output of this trial.

The multicentre structure, while a strength, also introduces potential heterogeneity. Despite harmonised imaging protocols and centralised molecular analysis, subtle differences in scanner hardware, software and site-specific procedures may contribute to variance in structural and functional magnetic resonance imaging metrics. Similarly, although biospecimen collection and processing were standardised and key assays centralised, residual inter-site variability in pre-analytical handling cannot be fully excluded, as well as deterioration during storage or shipment of the materials.

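### Non-imaging group comparisons name tests without a centre term, although recruitment and matching were by centre and the imaging analyses model site

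*Protocol article*

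**What the plan says.** Under Subjects recruitment, three centres took part and "Each centre enrolled a group of patients with HFEM or CM and a group of age- and sex-matched healthy subjects". No matching ratio is given.

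Under Descriptive and inferential statistics, "Quantitative variables were compared using the cross-sectional Mann–Whitney test", with chi-square or Fisher tests for categorical variables; a p value below 0.05 "was considered statistically significant". Of the control comparison it says "Variables were also compared between healthy controls and migraine patients, stratified for gender and diagnosis". The responder comparison listed there has no stated stratification.

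Centre appears in one place. Under Acquisition protocol, "scanner site was explicitly modelled as a covariate in all group-level neuroimaging analyses". For biological samples, Limitations and future directions concedes that "residual inter-site variability in pre-analytical handling cannot be fully excluded".

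Mitigation of confounding factors lists age, sex, subtype and other clinical variables that "were systematically collected and evaluated as potential confounders"; centre is not in that list. For epigenetics it adds that "known determinants of DNA methylation variability, including age, sex, medication exposure, and lifestyle-related factors such as smoking habits, were considered during statistical analyses", with batch correction where appropriate. The CGRP cut-off analysis is a generalised linear model with clinical and demographic covariates.

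**The concern.** A factor used to build the groups should normally stay in the analysis. Group matching does not call for a paired test, but it does call for centre to be a stratum or a covariate. The article accepts this for imaging and names rank and contingency tests elsewhere that, as described, have no centre term and cannot adjust for the listed confounders.

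Two things can then go wrong. If patients and controls have the same ratio in every centre, a centre shift in a marker only adds noise, so the test becomes conservative and loses power. If the ratios differ, the shift is partly read as a group difference. Responder status is an outcome, so responder numbers per centre are not fixed by design. In a biomarker-discovery study, a candidate that reflects sample handling at one site is a costly false lead.

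**Working it through.** **Inputs.** From Sample size calculation: 168 patients and 51 controls. From Subjects recruitment: three centres. From Descriptive and inferential statistics: the 5% level, taken here as two-sided because the article does not say. The article gives no centre means and no centre sizes, so those below are assumptions. It has no figure of its own on centre effects to reproduce.

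**Effect used for power.** (1.96 + 0.842) × √(1/168 + 1/51) = 2.80 × 0.160 = 0.45 SD, the difference that a simple z test detects with 80% power.

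**Simulation.** Normal data, within-centre SD 1, 4,000 datasets per setting; Mann-Whitney ignoring centre against the van Elteren test.

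| Spread over the three centres | Centre means (SD) | Quantity | No centre term | Centre-stratified |
|---|---|---|---|---|
| Patients 56/56/56, controls 17/17/17 | 0, 0.5, 1 | power | 73% | 78% |
| Same | 0, 1, 2 | power | 55% | 77% |
| Patients 56/56/56, controls 25/16/10 | 0, 0.5, 1 | type I error | 11% | 4% |
| Responders 35/26/18, non-responders 18/27/35 | 0, 0.5, 1 | type I error | 22% | 5% |
| Responders 30/26/23, non-responders 23/27/30 | 0, 0.5, 1 | type I error | 6% | 5% |

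**Check by hand.** Let s = √(1/n₁ + 1/n₀), τ² = 1 + the between-centre variance, and δ = the difference in group means that arises from centre mix alone. The unadjusted test then rejects with probability of about 1 − Φ(1.96τ − δ/s) + Φ(−1.96τ − δ/s). For centre means 0, 0.5 and 1 in equal thirds, τ² = 1 + 0.167, so τ = 1.080 and 1.96τ = 2.117.

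- Equal ratios: δ = 0, giving 2 × [1 − Φ(2.117)] = 3.4%, below the nominal 5%.
- Controls 25/16/10: the control mean is (16 × 0.5 + 10 × 1)/51 = 0.353 and the patient mean 0.5, so δ = 0.147. With s = 0.160, δ/s = 0.92, giving 1 − Φ(1.20) + Φ(−3.04) = about 12%.
- Strong responder imbalance: means (26 × 0.5 + 18)/79 = 0.392 and (27 × 0.5 + 35)/80 = 0.606, so δ = 0.214. With s = 0.159, δ/s = 1.35, giving about 22%.
- Mild responder imbalance: means 0.456 and 0.544, so δ = 0.088 and δ/s = 0.56, giving about 6%.

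The hand results agree with the simulation to about one percentage point.

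**Sensitivity to the size of the shift.** With equal ratios and steps between centres of 0, 0.25, 0.5 and 1 SD, the unadjusted test had power of 78%, 77%, 72% and 56%. With patients 70/56/42 and controls 13/17/21, its type I error was 5.2%, 6.4%, 13.7% and 31.8%. Across these settings the stratified test stayed between about 5% and 6% for type I error.

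**Price of stratifying when centres do not differ.** Power was 77.9% unstratified and 77.6% stratified with even spread, and 76.0% against 74.0% with 70/56/42 against 13/17/21. Only a strong mismatch (84/56/28 against 9/17/25) cost more: 77.5% against 71.9%.

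**The case against.** Several points on the other side are sound.

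- A reader might infer that the plan pools everyone and ignores age. The text does not support that. The control comparison is stratified by gender, itself a matching factor, and by diagnosis. Age is considered for methylation, and demographic covariates enter the CGRP model. Age is also restricted to 25 to 55 years and matched, and no figure here shows an age effect.
- A reader might infer that false positives are inflated as a matter of course, or that imbalance is likely. Neither follows. Inflation needs centre differences and unequal ratios together. The strong responder split implies response rates of 35/53 = 66%, 26/53 = 49% and 18/53 = 34% under one drug and common eligibility criteria. Biochemical and genetic assays are centralised in Pavia and methylation in Barcelona, which limits centre shifts, although collection and first processing were local.
- The article does not expressly assign the Mann-Whitney test to methylation and defers the downstream methylation analysis. The responder comparison that it spells out next to that test concerns clinical, anamnestic, psychological and disability measures.
- Adjustment sets for secondary comparisons often sit in an analysis plan, and the primary objective is a cross-validated classifier that these tests do not decide.

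The last point does not dispose of the matter. The article is not silent: it names the tests, names the strata, and says where site is modelled. As written, that leaves centre out of the non-imaging comparisons.

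**Conclusion.** The concern holds in a limited form. No non-imaging comparison is said to include centre, although recruitment and matching were by centre and imaging models site. For the remaining univariate comparisons (cytokines, genotypes, clinical and psychometric variables, and group comparisons of CGRP), age is not tied to the named tests either.

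The consequence is conditional. With equal ratios it is a loss of power only: about 5 points at steps of 0.5 SD between centres and about 22 points at 1 SD. With unequal ratios, type I error at 0.5 SD steps runs from about 6% under mild responder imbalance to 22% under strong imbalance. If centres do not differ, there is no harm. All of this rests on assumed shifts, assumed splits and normal data. The tests are secondary and exploratory, so the change is advisable rather than critical.

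**What to change.** For the non-imaging patient-control and responder-non-responder comparisons, state a centre-stratified Wilcoxon (van Elteren) test, or a rank or linear regression with centre, age and sex. For categorical variables, state a Cochran-Mantel-Haenszel or exact test stratified by centre, or logistic regression with the same terms where counts allow. Regression is the easier route if sex is also to be kept: crossing three centres with two sexes leaves on average 51/6 = 8.5 controls per cell.

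Report the numbers per group and centre beside each comparison, so that a reader can see whether the ratios differ.

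The cost is analysis code: centre is known, and age and sex were collected. If centres do not differ, the loss of power is negligible with similar ratios and grows only if ratios are badly mismatched. Status of the study says that the stratified-group analysis is still ongoing and the baseline data are in their last revision, so the change can still be made.
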